**Methods:**

A three-arm randomized controlled trial will be conducted. Sixty-nine participants with CLBP will be recruited in a 1:1:1 ratio. Participants, assessor, and statistician will be blinded to group assignment. The PNE intervention will be adapted to the context of the participants. An experimental group (*n* = 33) will receive PNE in an in-group modality, the other experimental group (*n* = 33) will receive PNE in an individually modality and the control group (*n* = 33) will continue with usual care. Additionally, participants will be encouraged to stay active by walking for 20–30 min 3–5 times per week and will be taught an exercise to improve transversus abdominis activation (bracing or abdominal following). The outcome measures will be fear avoidance and beliefs, pressure pain threshold, pain self-efficacy, catastrophizing, pain intensity, and treatment expectation. Outcome measures will be collected at one-week before intervention, immediately post-intervention, and four-weeks post-intervention.

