### Intervention

The content of the intervention will be identical in the experimental groups. The only difference is that the PNE in the in-group modality (G1) is provided in groups of 3–5 participants, while in the individual modality (G2) it is provided directly to a single participant. The intervention has an active educational approach based on reconceptualizing the maladaptive beliefs that influence the fear-avoidance behavior of the participants through updated contents of the neuroscience of pain. This will be delivered in a single face-to-face session of approximately 60–80 min in the kinesic clinic of the Santo Tomás University and will be delivered through active participation encouraging synchronous discussion of the information and allowing note-taking. A break will be made in the middle of the session to allow the participants a break. Five key domains will be structured based on the Fear and Belief Avoidance Questionnaire (Table 1) which will serve as a guide for the sessions through a Powerpoint presentation. In addition, participants will be encouraged to stay active by walking for 20–30 min, 3–5 times a week and will be taught an exercise to improve the activation of the transverse abdominis (bracing or abdominal following). The PNE will be delivered by a physical therapist with four years of experience in this intervention. In addition, the same physical therapist will provide the therapy to both experimental groups to maintain the same patient-physical therapist relationship and not to influence the results due to this contextual aspect, so no adaptations were made for each group either.

**Table 1 table-1:** Summary content of pain neuroscience education.

**Dimension**	**Content**
Dimension 1: Approach	Introduction to the program.
	The objective of today’s session will be to contrast what we know about pain, with the scientific advances in rehabilitation through a conversation.
	Your opinion regarding each of the points that we will discuss is very important for your rehabilitation.
Dimension 2: Pain as protector (the big picture)	Pain as a multidimensional experience
	- Neurophysiology of pain: pain pathways, neuronal synapses, action potentials and pain perception. Gate of entry of pain.
	- Modulation of pain: explain the processes of facilitation and inhibition. The theory of gate control will be emphasized.
	- Acute pain and chronic pain: explain the differences between acute pain and chronic pain

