Dimension 3: Pain is not always an indicator of damage (pain ≠ damage)	Pain does not depend entirely on the state of the tissues.
	Imaging findings associated with aging are like wrinkles or gray hair.
	examples of pain in the absence of damage (eg headache)
Dimension 4: Movement as an opportunity for recovery (movement experience)	-Importance of movement
	-explain the relevance of movement from the plasticity and robustness of the human body.
	-Neuroplasticity of the nervous system: Explain neuroplastic changes due to experience and learning with an emphasis on positive changes through movement.
	benefits of movement in functionality
	progressive active strategies
Dimension 5: Recovery expectations	Concept of pain modulation from cognitions
	strategies to help manage pain, relaxation/breathing techniques, positive thinking

In addition, a brochure will be delivered with the main points of each of the domains and information capsules will be made to which the participants will have access (five 15-minute videos, one per domain). Participants will be instructed to record on a calendar the days they performed the walks, exercises, and read the brochure, and/or review the information capsules to assess compliance with the treatment and for each domain invent a metaphor or write how they would explain it to another person. This activity must be delivered in the second assessment.

The total time of the intervention will be 135–155 min for both groups.

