#### Randomization and blinding

Participants will be randomized in a 1:1:1 ratio between intervention and control arms using balanced group assignment with block randomization with permuted block size. An independent researcher will carry out the process of randomization through a web platform (http://www.randomizer.org) and will allocate concealment from patients and other investigators using sealed, opaque envelopes.

Participants, assessor, and statistician will be blinded to group assignment. Participants will only be informed that they will receive an educational intervention without indicating to which experimental group they will belong; the assessor will not be informed of the group to which the participants belong; and the identification data of the participants will be coded in the database before being sent to the statistician. However, the physical therapist who will perform the educational intervention will not be blinded.

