### Data analysis

#### Statistical approach

The analysis of the data will be blinded, as each subject and condition will be coded by a consultant who will not be involved in the investigation. SPSS software version 25.0 will be used for all analyzes (SPSS Inc. Armonk, NY, USA). Data will be reported as mean with SD or median with interquartile range. Statistical analyzes were performed on an intention-to-treat basis, with imputation of missing data using the average of the remaining participants.

Normality tests will be performed using the Shapiro–Wilk test given the number of subjects needed for each group. In addition, the homogeneity of variance and the sphericity of the data will be determined. In the case of not assuming any of these assumptions, the Green-Hausser correction will be used for the interpretation of subsequent analyzes. A three-way repeated measures ANOVA will be conducted to analyze both primary and secondary outcomes. The factors considered in this analysis will include time and intervention. Additionally, the third factor will encompass variables such as employment status, education level, or income. In case of significant interaction, a two-way repeated measures ANOVA (time (pre-post) × intervention (in-group PNE, individually PNE, no intervention)) will be performed for each employment status (employed or unemployed). Furthermore, a two-way repeated measures ANOVA (time (pre-post) × intervention (in-group PNE, individually PNE, no intervention)) will be performed for each educational level (high or low). Lastly, a two-way repeated measures ANOVA (time (pre-post) × intervention (in-group PNE, individually PNE, no intervention)) will be performed for income (≤USD 545, or >USD 545). If interactions are detected in any of the 2-way ANOVAs, a *post-hoc* analysis will be conducted using multiple pairwise comparisons employing a *t*-test corrected by Bonferroni. The significance level will be set at 5%.

A stepwise multiple linear regression will be performed to estimate the influence of changes in primary and secondary outcomes. In each model, adjustments will be made for employment status, educational level, and income. In this analysis, the aforementioned variables will be sequentially incorporated into each model.

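### Participants are declared blinded to group assignment although each one experiences the feature that defines the arm, and homework due at the second assessment may unmask PNE versus control to the assessor

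*Protocol article*

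**What the plan says.** Under Randomization and blinding, the protocol article declares that "Participants, assessor, and statistician will be blinded to group assignment"; the Methods paragraph of the abstract says the same. Two safeguards are given for the people concerned:

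- Participants: "Participants will only be informed that they will receive an educational intervention without indicating to which experimental group they will belong".
- Assessor: "the assessor will not be informed of the group to which the participants belong".

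The Intervention section says that the content is the same in both experimental arms and that only the setting differs: PNE in the in-group modality "is provided in groups of 3–5 participants, while in the individual modality (G2) it is provided directly to a single participant". For the third arm, the abstract says that "the control group (*n* = 33) will continue with usual care", while the Statistical approach section lists the levels of the intervention factor as "in-group PNE, individually PNE, no intervention".

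The Intervention section also asks participants to keep a calendar of walks, exercises, brochure reading and video viewing, and to compose a metaphor or explanation for each PNE domain. It adds: "This activity must be delivered in the second assessment". No recipient is named. The Limitations section identifies the treating therapist as unblinded and nobody else.

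**The concern.** A blinding statement tells readers how far to trust outcomes that can shift with knowledge of treatment. Here the treatment contrast is the delivery setting itself, or the absence of a session, and neither can be hidden from the person receiving it.

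The outcomes are sensitive to this. FABQ is a questionnaire about the participant's own beliefs. PSEQ, PCS, NRS and TEX-Q are also answered by the participant, and the pressure pain threshold depends on when the participant reports pain. In effect the unblinded participant is the outcome assessor for the primary endpoint. If the declaration is carried into the results paper, readers would rate the risk of performance and detection bias too favourably.

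The assessor's blinding matters mainly for algometry, where an operator takes the measurement. Homework that exists only because someone received PNE, handed in at an outcome visit, is a possible leak.

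**Working it through.** The plan gives no figure to reproduce on this point. The check sets the sections side by side, followed by one small illustration.

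**Step 1. Can participants be blind to assignment?**

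- In-group arm: a session with 3–5 participants (Intervention).
- Individual arm: a session alone with the therapist (Intervention).
- Control arm: "will continue with usual care" (abstract), or no intervention (Statistical approach). On either description, no PNE session is described for this arm.

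Each arm is defined by something the participant sees directly. The only safeguard is not naming the arm. That works until the session takes place, or fails to take place, and every post-baseline outcome is measured afterwards. What can remain masked is the directional hypothesis, or the fact that other arms exist.

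**Step 2. Does the stated information fit all three arms?** Participants are said to be told that they will receive an educational intervention. This fits the two PNE arms. It does not fit a control arm for which no PNE is described. If the sentence was meant for the PNE arms only, the article gives no masking procedure for controls.

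**Step 3. What could the homework reveal?** Inputs: 1:1:1 allocation (Randomization and blinding) and identical content in both PNE arms (Intervention). Assumptions, none of them stated in the article: the assessor sees the homework, every PNE participant returns it, and no control does.

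- Naming the arm, without homework: 1/3 (33%).
- Naming the arm, with homework: a control is always recognised; a PNE participant is recognised as PNE, but the setting is still a guess. So 1/3 × 1 + 2/3 × 1/2 = 1/3 + 1/3 = 2/3 (67%).
- PNE versus control: known for everyone (100%).
- In-group versus individual, among PNE participants: 1/2 before and 1/2 after.

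So the homework can expose PNE versus control, but carries no information on modality unless a participant mentions the setting.

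**Step 4. Timing.** This route presupposes that the second assessment is one week after the session, as in Data collection and management. The abstract places it immediately after the intervention, when little homework could yet exist.

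**The case against.** Several points on the other side are fair.

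- Participant blinding is unattainable when the setting is the treatment, so the design itself is not at fault. This stands, but it is a reason to describe participants as unblinded, not to declare them blinded.
- The authors did not ignore expectation. The Limitations section says that it can significantly influence the results, and TEX-Q measures it. This also stands, yet the section does not connect expectation to participants knowing what they received.
- A reader might infer that the plan itself breaks the assessor's blinding. The documents do not support this. They say when the homework is due, not who receives or reads it. That detail could be in the full trial protocol, which is listed as supplemental and not shown.
- A reader might also infer that the homework discloses the arm. It does not: with identical content it cannot separate in-group from individual PNE, which is the comparison in the first objective and the main hypothesis.
- A reader might infer that controls are to be told something untrue. The sentence does not say that it covers all participants, and its reference to an experimental group may limit it to the PNE arms. The wording is ambiguous; a false statement to controls is not established.
- The abstract leaves unclear whether the walking and exercise advice also reaches controls. If it does, activity records might not be unique to PNE, although the domain metaphors would be.

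**Conclusion.** The declaration that participants are blinded is wrong as written, because the article's own description of the arms contradicts it. This affects every participant and all the self-reported outcomes (FABQ, PSEQ, PCS, NRS, TEX-Q), and algometry in so far as it depends on the participant's response. The exposure is greatest for PNE versus control, where one side has a session and the other has none. It also exists between the two PNE arms. A fuller document could not make the statement true, so this is not a matter of detail left out of an article. The direction and amount of bias cannot be derived from what is given.

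The assessor point is narrower: a possible, unconfirmed route by which PNE versus control may become known, with no stated step to close it. It rests on the assessor handling the homework and on the one-week timing.

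No sample size, analysis method or planned comparison needs to change. What changes is the blinding statement, a step in trial conduct, and how firmly PNE-versus-control results can be stated.

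**What to change.** 1. In the abstract and under Randomization and blinding, state that participants and therapist are not blinded (participants at most unaware of the hypothesis), and that only the assessor and the statistician are.
2. Say what participants in each arm are told, and reword the reference to an educational intervention so that it is accurate for controls.
3. Have calendars and metaphors returned to someone other than the assessor, for example in a sealed envelope to the independent researcher who runs the randomisation and already knows the allocation.
4. Add participant unblinding to the Limitations section, linked to the expectation effect already noted there, and temper the PNE-versus-control conclusions accordingly.

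The cost is wording and a change in who takes the homework; no extra staff are needed. The drawback is that the stated blinding becomes less favourable.

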#### Ethics

The study was approved by the Central-South Macrozone Ethics Committee of the Universidad Santo Tomás, Chile, according to the Declaration of Helsinki for biomedical research (exp-23-13). All participants will provide written informed consent.

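### The information said to keep participants blinded is either untrue for the control arm or gives no basis for blinding it, so self-reported contrasts with control are open to expectation bias

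*Protocol article*

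**What the plan says.** All statements are in the protocol article.

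- **Blinding claim** (Randomization and blinding): "Participants, assessor, and statistician will be blinded to group assignment". No arm is excepted.
- **How it is achieved** (same section, next sentence): "Participants will only be informed that they will receive an educational intervention without indicating to which experimental group they will belong".
- **Who is randomised** (same section): "Participants will be randomized in a 1:1:1 ratio between intervention and control arms".
- **What controls get**: the abstract's Methods say the control group "will continue with usual care". The Statistical approach section gives the levels of the intervention factor as "in-group PNE, individually PNE, no intervention".
- **Who gets PNE** (Intervention): "The content of the intervention will be identical in the experimental groups". That section then defines the in-group arm (G1) and the individual arm (G2). It gives the control arm no session, brochure or videos.

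**The concern.** The blinding section does not merely leave out a detail. It states what participants are told, says they are told only that, and rests the blinding claim on it. The statement does not fit an arm that receives no education.

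The outcomes make this matter. The primary outcome, the Fear Avoidance Beliefs Questionnaire (FABQ), is self-reported. So are pain self-efficacy (PSEQ), catastrophizing (PCS), pain intensity (NRS) and treatment expectation (TEX-Q). The Limitations section itself accepts that expectations of the therapy can influence the results considerably. Controls who were led to expect education, or who simply see that they received none, may answer differently from people who attended a session. Their TEX-Q scores would also be hard to set beside those of the PNE arms, because it is unclear which treatment they refer to.

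**Working it through.** The point rests on comparing the sections. The arithmetic is small.

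**1. Share affected.** Under 1:1:1 allocation the control share is 1/3. The article gives three different sample sizes, and the share is the same under each:
- 33 per arm in the abstract: 33/99 = 1/3
- 69 in total in the abstract: 23/69 = 1/3
- 20 per group in the Sample size section: 20/60 = 1/3

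The disagreement between these totals is a separate matter and nothing here depends on it.

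**2. The two readings of the information sentence.**

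| Reading | Told to controls | Received by controls | Consequence |
|---|---|---|---|
| It covers everyone randomised, as in the blinding sentence before it | That they will receive education | Usual care or no intervention | Untrue for 1/3 of participants, and controls can see that no session took place |
| It covers only the two experimental groups | Not stated | Usual care or no intervention | The blinding claim still covers all participants but has no mechanism for controls |

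Neither reading makes the section consistent with the abstract, the Intervention section and the Statistical approach section together.

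**3. Which contrasts are exposed.**
- In-group versus individual PNE: both arms receive education, so the statement is true for both. The first objective and the stated hypothesis about format are not touched by this conflict.
- Either PNE arm versus control: exposed on FABQ, PSEQ, PCS, NRS and TEX-Q.

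**4. Direction.** Disappointed or less hopeful reporting by controls would make them look worse, which favours PNE. This is the most plausible direction, but the document gives no figure from which to estimate a size.

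Drop-out has no such clear direction. If dissatisfied controls with worse scores leave, the remaining controls look better and the difference shrinks. The planned imputation, by the average of the remaining participants, can also shrink it. Suppose a fraction d of controls is lost at random, nobody else is lost, and the average is pooled over arms. With p the mean in the PNE arms, c the mean in controls and M the pooled mean, the estimated difference is

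p − [(1 − d)c + dM] = (p − c) − d(M − c).

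M lies between c and p, so the result is closer to zero than p − c. If the average is taken within arm, the difference equals that among completers. The article does not say which average is meant.

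**The case against.** The strongest reply is that the sentence speaks of the experimental group, a term the article otherwise keeps for the two PNE arms. On that reading it only withholds the delivery format from people who do receive education, and it is true. This is a fair reading and rules out calling the sentence plainly false. It does not rescue the section, because the blinding claim just before it covers all participants and nothing else is offered to support it for controls.

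A second reply is that controls may receive something. The abstract mentions walking advice and an abdominal exercise directly after describing the control arm, whereas the Intervention section places both within the PNE intervention. The ambiguity is real, but the analysis section still labels the arm as no intervention.

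A third reply is that a journal article condenses the protocol. The participant information, the full trial protocol and both figures are not shown. This reply stands against two stronger conclusions that a reader might draw:

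- *That controls give misinformed consent.* The Ethics section says only "All participants will provide written informed consent". What they are told at consent cannot be judged from the text shown, and the information sheet may describe all three arms correctly.
- *That nothing is offered to controls after follow-up.* The text shown describes no such offer, but the full protocol may contain one.

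A reader might also infer that control drop-out is built into the design, or that it would inflate the effect. The article gives a single drop-out allowance of 10%, says nothing about loss by arm, and, as shown above, loss of controls could as well reduce the difference.

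**Conclusion.** The point holds as a conflict between sections. The claimed participant blinding depends on a statement that is untrue for one third of participants if it covers everyone. If it covers only the PNE arms, the claim is unsupported for that third. In both cases the PNE-versus-control contrasts on self-reported outcomes cannot be treated as participant-blinded and are open to expectation bias, most plausibly in favour of PNE. The comparison of in-group with individual PNE is not affected.

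This assumes that controls receive no education before the four-week assessment, as the abstract, Intervention and Statistical approach sections indicate. It does not establish that consent is in fact misinformed or that drop-out is built in, and it says nothing about the size of any bias. It should be corrected, but it does not call the whole design into question.

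**What to change.** Reconcile the Randomization and blinding section with the abstract, the Intervention section and the Statistical approach section, in one of two ways:

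1. State truthfully that allocation is by chance to group education, individual education or continued usual care, with the hypothesis about which is better withheld.
2. State that controls receive the brochure and videos, already planned for the PNE arms, after the four-week assessment, so that the announcement of education is true for every arm.

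Under either option, limit the participant-blinding claim to the study hypothesis, and say that contrasts with control on self-reported outcomes will be interpreted as not participant-blinded. Check that the participant information agrees.

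The cost is rewording, with an ethics notification if the participant information changes. Sample size and analysis stay as they are, and releasing materials that will already exist after the last visit costs little. The downside is that controls know they may get no session during follow-up. The expectation difference between PNE and control therefore remains, but it is declared.
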